### Sample size

Because the FITT study in the US was still underway at the time of writing this protocol, sufficient data on the unplanned-use of the health care system was not available. However, considering the high prevalence of stroke recurrence, emergency visits because of medications errors, falls and depression in the stroke population, we estimated a mean number of unplanned-use equal to three in the first six months post-stroke with a standard deviation of one unplanned-use. If we aim to decrease unplanned-use of the health care system by 10%, a sample size of 175 participants in each group is necessary with an alpha level set at 5% (for a bilateral test) and a power of 80%. A sample size of 57 individuals per group would be required to detect a two-point difference in the Quality of Life Index global score using data from a previous study [67] on quality of life of individuals with stroke (n = 72; mean = 20.91 ± 3.8). Given these estimates and considering a potential loss to follow up of 10%, a total sample of **384 individuals **is targeted for recruitment. These numbers are sufficiently large (using same parameters, required n < 65/group for participation and depression) to allow for large effect size of secondary outcomes and to do subgroup analysis according to comorbidity level.

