**Method/Design:**

We will recruit 384 adults who meet inclusion criteria for a first mild stroke across six Canadian sites. Baseline measures will be taken within the first month after stroke onset. Participants will be stratified according to comorbidity level and randomised to one of two groups: YOU CALL or WE CALL. Both interventions will be offered over a six months period. Primary outcomes include unplanned use of heath services for negative event (frequency calendar) and quality of life (EQ-5D and Quality of Life Index). Secondary outcomes include participation level (LIFE-H), depression (Beck Depression Inventory II) and use of health services for health promotion or prevention (frequency calendar). Blind assessors will gather data at mid-intervention, end of intervention and one year follow up.

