### The research objective

The purpose of this study is to assess the effectiveness, for individuals who experience a first "mild" stroke, of a sustainable, low cost, multimodal support intervention (comprising information, education and telephone support) - "***WE CALL***" compared to a passive intervention (providing the name and phone number of a resource person available if they feel the need to) - "***YOU CALL***", on two primary outcomes: unplanned-use of health services for negative events and quality of life. Secondary outcomes include participation level, depressive symptoms, and planned-use of health services for health promotion and secondary prevention. A secondary objective is to *explore *the contribution of potential explanatory variables such as age, gender, living alone versus with a significant other, comorbidity level and access (or not) to a secondary stroke prevention clinic, on outcomes. We hypothesize that the provision of the *"WE CALL" *intervention over the first six months post-stroke, compared to the *"YOU CALL" *will have three positive effects persisting 6 months beyond the intervention period:

1) A decreased unplanned-used of health services for negative events;

2) An improved quality of life;

3) Less depressive symptoms, a better participation in daily activities and social roles, and an increase in planned health visits for promotion and secondary stroke prevention;

In addition, we hypothesize that:

4) Participants with higher comorbidity level will benefit more from the active intervention given the increased complexity of their health status and,

5) Participants with access to secondary stroke prevention (SPC) clinic will benefit more from the intervention than those without SPC access.

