2. A number of **quality of life **tools were reviewed (e.g. SF-36, Stroke Impact Scale, Quality of Life Index) and the tool chosen was a compromise between psychometric properties and adequacy of content for mild stroke. The 32 item questionnaire **Quality of Life Index **(QLI) [47] which was developed from Ferran's conceptual model of quality of life and which has been used with a stroke clientele [48] was chosen as the primary outcome. Each item of the QLI as relating to four life domains (health and functioning, socio-economic, psychological/spiritual and family), is evaluated in terms of satisfaction and importance on a six-point scale. Scores for each domain and a global score are expressed from 0-to-30, with a higher score indicating a better quality of life. These four life domains relate well with the main issues covered through the WE CALL intervention. Its has shown to have adequate psychometric properties (concurrent validity, test-retest reliability and high internal consistency: α = 0.90) [47] and thus should be responsive to therapy-induced change [49,50]. A one-point difference was observed in the first six months post-stroke descriptive follow-up (n = 63) for an effect size of 0.33 [51]. A two-point difference is considered a clinically meaningful change leading to a moderate effect size of 0.66. The **EQ-5D **which is composed of 5 items rated on a three-level scale [52] is also being completed as this questionnaire provides utility estimates needed to performed cost-utility analysis The EQ-5D is one of the recommended instruments by the Canadian Agency for Drugs and Technologies in Health (CADTH) [53].

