### Planned statistical analyses

First, baseline characteristics of the sample will be presented using descriptive statistics. All analysis of primary and secondary available outcomes will be realised on an intention-to-treat basis thus respecting group allocation irrespective of whether participants received the intervention or not. The primary endpoint for analysis is the end of the intervention: six months period. A between group comparison on the difference in scores between six months measurement and baseline, between "we call" and "you call" will be made using an independent sample t-test for both primary and secondary outcomes. Effect size of the differences with their 95% confidence interval will be reported. As we anticipate unplanned-use of health services to not be normally distributed (we might end up with many 'zero' negative event), we plan to confirm parametric statistics with non-parametric testing. Also, repeated measures analysis will be realised using the four times of measurements (baseline, three months, six months and one year) where the between-subject factor is the intervention type, the within-group factor is time and their interaction provides the intervention effectiveness, including the one-year follow up phase. Also, multiple linear regression analyses will be used to explore the contribution of the potential explanatory variables (including group assignment, age, gender, living alone versus with a significant other, comorbidity level, *etc*.) on change in primary and secondary outcomes.

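### Two primary outcomes are each sized at the full two-sided 5% with no stated success rule or alpha allocation, and the abstract and main text disagree on whether EQ-5D is primary

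*Protocol article*

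**What the plan says.** The research objective section sets out to judge the intervention "on two primary outcomes: unplanned-use of health services for negative events and quality of life". Hypotheses 1 and 2 in that section take these one at a time.

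The sample size section assumes, for unplanned use, "a mean number of unplanned-use equal to three in the first six months post-stroke with a standard deviation of one unplanned-use". It aims for a 10% reduction and arrives at 175 per group, "with an alpha level set at 5% (for a bilateral test) and a power of 80" per cent. It then gives 57 per group for a two-point difference in the QLI global score, with SD 3.8, and does not repeat the alpha. Recruitment is set at 384, allowing for 10% loss.

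The planned statistical analyses section takes six months as the primary time point. The between-group comparison "will be made using an independent sample t-test for both primary and secondary outcomes". No section states a testing order, a division of alpha, or a rule for calling the trial positive.

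On the quality-of-life instrument, the abstract's Method/Design paragraph lists as primary "quality of life (EQ-5D and Quality of Life Index". The detailed description of outcome measures says that the QLI "was chosen as the primary outcome". It explains the inclusion of EQ-5D by saying that "this questionnaire provides utility estimates needed to performed cost-utility analysis".

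**The concern.** With two primary outcomes, two separate tests and 5% spent on each, a reader cannot tell what result would make the trial positive. If one significant outcome is enough, the 5% in the sample size section is not the error rate of the trial's main conclusion. Both outcomes are offered as evidence that the same intervention is effective, so one chance finding could carry that claim.

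The instrument conflict adds a second opening. EQ-5D and the QLI are both collected. With the abstract and main text at odds, either could be presented as the primary quality-of-life result once the data are known.

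**Working it through.** **1. Do the plan's own sample sizes imply a full 5% for each outcome?**

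Inputs from the sample size section: unplanned use, mean 3, SD 1, 10% reduction, so a difference of 0.3; QLI, difference 2, SD 3.8; power 80%; two-sided alpha 5%. Formula per group: n = 2 × SD² × (z for alpha/2 + z for power)² / difference².

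- Unplanned use: 2 × 1 × (1.960 + 0.842)² / 0.09 = 174.4, rounded up to 175. Stated: 175.
- QLI: 2 × 14.44 × (1.960 + 0.842)² / 4 = 56.7, rounded up to 57. Stated: 57.
- The exact t-test gives 175.4 and 57.6.
- At 2.5% each, the t-test would need 212.5 and 69.9.

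Both stated figures reproduce at 5% and neither does at 2.5%. So the QLI was also sized at the whole 5%, although its sentence does not say so.

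**2. Family-wise error if success on either outcome counts (assumed)**

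- Independent tests: 1 − 0.95² = 0.0975. The upper bound for any dependence is 0.05 + 0.05 = 0.10.
- Correlated test statistics, bivariate normal (the documents give no correlation, so this is an assumed range):

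| Correlation | Chance of at least one false positive |
|---|---|
| 0.3 | 9.5% |
| 0.5 | 9.1% |
| 0.7 | 8.3% |

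- Counting only false claims in favour of WE CALL, independent tests: 1 − 0.975² = 4.9%, against 2.5% for a single test.

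**3. Power at other alpha levels with the planned recruitment**

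Evaluable per arm: 384 × 0.9 / 2 = 172.8, taken as 172. Standardised effects: 0.3 / 1 = 0.30 for unplanned use and 2 / 3.8 = 0.526 for the QLI. Two-sample t-test:

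| Two-sided alpha | Unplanned use | QLI |
|---|---|---|
| 0.05 | 79.2% | 99.8% |
| 0.045 | 77.9% | – |
| 0.025 | 70.2% | 99.6% |
| 0.005 | – | 98.0% |

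The trial is sized on unplanned use, so the QLI has power to spare. An equal split costs unplanned use 9 points (79.2 − 70.2). A 0.045/0.005 split costs it 1.3 points (79.2 − 77.9).

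**4. Which quality-of-life measure is primary?**

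The abstract lists two. The outcome description names the QLI and gives EQ-5D a utility role, the sample size section sizes only the QLI, and the economic paragraph uses EQ-5D to estimate QALYs. The main text is consistent with itself; the abstract is the outlier.

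**The case against.** The strongest defence is that this is a condensed article and that test order or alpha allocation is commonly left to a statistical analysis plan, which is not shown. Sizing each outcome at 5% is also what a fixed-sequence plan or a both-required rule would do, and either would hold 5% with the same 384 participants. Some wording leans towards both being required: the closing summary of the Background asks about reducing unplanned use and improving quality of life together. Under a both-required rule there is no inflation.

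Much of this stands. The sample sizes show how the outcomes were sized, not how success will be declared. A reader might infer that the plan fixes an either-outcome rule and therefore an error rate of 10%. The document supports neither step: no section states that rule, and the 10% also needs independent tests or the worst-case bound. Equally, the separately numbered hypotheses and separate t-tests do not establish a both-required rule.

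A reader might also count EQ-5D as a third primary outcome and quote 1 − 0.95³ = 14.3%. That count rests on the abstract alone, and the main text resolves it to the QLI.

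The defence does not remove the whole point. An analysis plan that split alpha equally would contradict the published power, as the third step of the working shows, so the choice bears on the sample size statement. And no other document can remove the conflict over EQ-5D from the published text.

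**Conclusion.** The point holds in a limited form. The main text has two primary outcomes, each sized at the full two-sided 5% and each compared by its own t-test, with no stated success rule or alpha allocation. If success on either counts, the family-wise error is up to about 10%, and roughly 8% to 9.5% under the assumed positive correlations. If both must succeed, or the tests are run in a fixed order, it stays at 5% or below. The document does not say which applies.

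The abstract's listing of EQ-5D as primary is a separate, definite inconsistency with the main text, and it should not be used to enlarge the error figure.

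**What to change.** 1. Correct the abstract so that the QLI global score is the only primary quality-of-life endpoint and EQ-5D serves the cost-utility analysis.
2. State, before analysis, one rule that holds the family-wise error at 5% over unplanned use and the QLI. Any of these would do:
   - a weighted Holm procedure, for example 0.045 for unplanned use and 0.005 for the QLI, passing alpha on after a rejection;
   - a fixed sequence with the order named;
   - an explicit rule that both outcomes must be significant.
3. Restate power under the chosen rule. With 0.045/0.005 and 172 evaluable per arm, the first-step figures are 77.9% and 98.0%. If the QLI is rejected first, unplanned use is tested at the full 0.05, so 77.9% is the lower figure for that outcome. If both are required, the joint power at 0.05 each is at least 79.2 + 99.8 − 100 = 79.0%. An equal split is the costly option: holding 80% power for unplanned use at 0.025 would need about 212 per group, or 424 / 0.9 = 472 recruited.

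The change is to wording. Under the weighted option it costs about one point of nominal power on unplanned use and no extra participants. The article reports that enrolment was still under way, so the rule could be fixed before any outcome comparison.

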### Planned statistical analyses

First, baseline characteristics of the sample will be presented using descriptive statistics. All analysis of primary and secondary available outcomes will be realised on an intention-to-treat basis thus respecting group allocation irrespective of whether participants received the intervention or not. The primary endpoint for analysis is the end of the intervention: six months period. A between group comparison on the difference in scores between six months measurement and baseline, between "we call" and "you call" will be made using an independent sample t-test for both primary and secondary outcomes. Effect size of the differences with their 95% confidence interval will be reported. As we anticipate unplanned-use of health services to not be normally distributed (we might end up with many 'zero' negative event), we plan to confirm parametric statistics with non-parametric testing. Also, repeated measures analysis will be realised using the four times of measurements (baseline, three months, six months and one year) where the between-subject factor is the intervention type, the within-group factor is time and their interaction provides the intervention effectiveness, including the one-year follow up phase. Also, multiple linear regression analyses will be used to explore the contribution of the potential explanatory variables (including group assignment, age, gender, living alone versus with a significant other, comorbidity level, *etc*.) on change in primary and secondary outcomes.

The economic impact of the two interventions "We call" and "You call" will be estimated with a cost-utility analysis. As one of the main outcomes of these interventions is their impact on quality of life, a cost-utility analysis represents the preferred type of economic evaluation. In a cost-utility analysis, outcomes are measured in terms of Quality Adjusted Life Years (QALYs) gained. In this study, QALYs will be estimated using the EQ-5D results measured at baseline, three months, six months and one year post-stroke. For this cost utility-analysis all costs associated with each intervention will be measured. These include the costs associated with the THCP for the "We call" group, costs associated with the THCP when contacted by a "You call" participant, cost of material provided and all costs of related health care resource utilisation (physician visits, emergency visits, use of other health care professionals, etc) for either negative event or secondary prevention. Cost associated with the use of the QLI, EQ-5D, LIFE-H, BDI-II and other procedures related to the study itself but not to the interventions will not be included. Result of this cost-utility analysis will be expressed in terms of incremental cost per QALY.

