### Interventions

**WE CALL **is a multimodal (Telephone, Internet and Paper) support intervention provided to participants randomly allocated to the "**WE CALL**" group. The telephone component of the intervention is based on the Family Intervention Telephone Tracking model (FITT), where pilot data shows promising effectiveness in the US ([name], Miller I, Weiner D, Guilmette T, Mukand J, Evans RL, et al. Family Intervention: Telephone Tracking (FITT): A preliminary stroke outcome study. Submitted). The FITT focuses on reinforcing problem solving skills through counselling and favours the use of available community resources. Issues pertaining to secondary prevention and adaptation are included. Each telephone interaction focuses on any new, or ongoing issues as well as six key areas (i) family functioning, (ii) depression, (iii) neurocognitive functioning, (iv) functional independence, (v) physical health and vi) individualised risk factors.

Participants are being asked how they are doing with these six key areas. For example, when discussing functional capacity, one important issue may be driving. Did they receive any advice in regards to driving? Do they have the required abilities to drive safely? Do they need an assessment or re-training? As an intervention, they could be referred to the *StrokEngine *module specifically on driving after a stroke (via Internet or through hard copies) and specific concerns could be individually discussed over the phone. Each specific issue is addressed during the next call to ensure active involvement. Participants of this group will be called by the Trained Health Care Professional (THCP) on a weekly basis for the first two months, bi-weekly during the third month, and monthly for the last three months of the intervention. It is estimated that each intervention call should last between 15 - 20 minutes ([name], Miller I, Weiner D, Guilmette T, Mukand J, Evans RL, et al. Family Intervention: Telephone Tracking (FITT): A preliminary stroke outcome study. Submitted). Participants are encouraged to contact the THCP between intervention calls, should they feel the need to. If the THCP is unavailable, the participant is invited to leave a voice message and the THCP will contact them within the day, with the exception of weekends. The frequency and content of these additional calls is documented.

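### The named six-month comparison is an available-case t-test on change scores, so it can be biased if loss differs between the arm that is called and the arm that is not

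*Protocol article*

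**What the plan says.** All references are to the protocol article.

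- **Analysis set (Planned statistical analyses).** "All analysis of primary and secondary available outcomes will be realised on an intention-to-treat basis", a label that the same sentence explains as "thus respecting group allocation irrespective of whether participants received the intervention or not".
- **Main comparison (same section).** The primary endpoint is at six months. The contrast is "A between group comparison on the difference in scores between six months measurement and baseline", and it "will be made using an independent sample t-test for both primary and secondary outcomes". A non-parametric test is planned as confirmation because visit counts may be skewed.
- **Additional analysis (same section).** A "repeated measures analysis will be realised using the four times of measurements": baseline, three months, six months and one year. It is described by its between-subject and within-subject factors only.
- **Expected loss (Sample size).** The target of 384 was set "considering a potential loss to follow up of 10" per cent. No figure is given by arm.
- **Contact (Interventions).** WE CALL participants are telephoned "on a weekly basis for the first two months, bi-weekly during the third month, and monthly for the last three months of the intervention". YOU CALL participants have contact only if they start it.

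**The concern.** A t-test on the change between baseline and six months needs both values. A participant with a three-month QLI score but no six-month score therefore contributes nothing to the comparison named for the primary endpoint. Recruiting more people replaces the lost numbers but not the lost people.

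The between-arm difference is biased when the product of loss rate and gap (how far lost participants differ from those observed) is not the same in both arms. The design gives a reason to consider that possibility. One arm receives about 13 to 14 scheduled calls over six months (8 or 9 weekly, 2 in the third month taking bi-weekly as every two weeks, and 3 monthly), and the other receives none. The events that the protocol expects to drive unplanned use, such as recurrence, falls and depression, could also plausibly make people stop responding. The target for visits is small, at 0.3, so even a modest bias is a visible share of it.

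**Working it through.** **Inputs from the Sample size section.** Visits: mean 3, SD 1, target reduction 10%, so 0.10 × 3 = 0.3 visits. QLI: SD 3.8, target 2 points. Two-sided alpha 5%, power 80%, overall loss 10%, total 384, so 192 per arm.

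**Reproducing the plan's figures.** n per group = 2 × SD² × (1.96 + 0.8416)² / difference².
- Visits: 2 × 1 × 7.849 / 0.09 = 174.4, so 175, as stated.
- QLI: 2 × 14.44 × 7.849 / 4 = 56.7, so 57, as stated.
- Total: 350 × 1.1 = 385, or 350 / 0.9 = 389. The stated 384 is close to the first.

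**What the loss allowance achieves.** With 10% lost, 192 × 0.9 = 172.8 per arm remain, and power for 0.3 visits is 79.6%. Power is essentially kept. This calculation does not address bias.

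**Bias formula.** In an arm with loss fraction m, the observed mean minus the full mean is m × (mean of observed − mean of lost). The bias in the treatment difference is this quantity in WE CALL minus the same quantity in YOU CALL. With the same gap G in both arms, its size is |m(WE) − m(YOU)| × G.

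**Assumptions, not in the documents.** Loss splits by arm as shown, averaging 10%. Lost participants do worse than observed ones by 0.5 to 1 SD, which is 0.5 to 1 visit or 1.9 to 3.8 QLI points. For QLI the gap must be in *change*, because the test subtracts baseline. The plan's 3.8 describes a score level and stands in here for the SD of change.

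**Worked case, 5% lost in WE CALL and 15% in YOU CALL.**
- Visits: 0.10 × 0.5 = 0.05 and 0.10 × 1 = 0.10. As shares of 0.3 these are 17% and 33%.
- QLI: 0.10 × 1.9 = 0.19 and 0.10 × 3.8 = 0.38. As shares of 2 these are 10% and 19%.
- Type I error for visits: 182.4 and 163.2 are observed, so SE = √(1/182.4 + 1/163.2) = 0.108. A bias of 0.05 to 0.10 raises the two-sided error from 5% to 7.5–15.3%. QLI gives the same, because the gaps are the same in SD units.

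| Loss WE / YOU | Bias, visits (share of 0.3) | Bias, QLI points (share of 2) | Type I error |
|---|---|---|---|
| 10% / 10%, same gap | 0 | 0 | 5.0% |
| 7.5% / 12.5% | 0.025–0.05 (8–17%) | 0.10–0.19 (5–10%) | 5.6–7.5% |
| 5% / 15% | 0.05–0.10 (17–33%) | 0.19–0.38 (10–19%) | 7.5–15.3% |
| 0% / 20% (extreme) | 0.10–0.20 (33–67%) | 0.38–0.76 (19–38%) | 15.2–45.5% |
| 10% / 10%, gaps of opposite sign | 0.10–0.20 (33–67%) | 0.38–0.76 (19–38%) | 15.3–46.0% |

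**Direction.** If those lost do worse and YOU CALL loses more, the observed YOU CALL group looks too healthy and the bias runs against WE CALL. If WE CALL loses more, it runs in favour of WE CALL.

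**The case against.** Several points on the other side stand.

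- **The label.** A reader might infer that calling an available-outcome analysis intention-to-treat is a contradiction. It is not. The protocol says what it means, analysis by allocated arm whatever was received, and says openly that outcomes are those available. Participants who did not take up the calls but have outcome data are kept.
- **Three-month data.** A reader might infer that these are thrown away. They are not, since the repeated measures analysis uses all four time points. What remains is that this analysis is additional to the t-test and that the text does not say incomplete records are kept in it.
- **Partial calendars.** Nothing says that they are dropped. The Design section lists quality of life, participation and depression at baseline, not service use, so the change-score argument does not carry over directly to visits.
- **Outcome-related loss.** Such loss does not by itself bias the comparison. The same rate and gap in both arms give no bias in the difference.
- **Loss by arm.** No figures are given. Assessors are blind to group, one assessment schedule serves the whole study, and frequent calls might tire people as easily as retain them.
- **Size.** A reader might infer a bias as large as the whole 0.3-visit effect. At 5%/15% loss that needs lost participants to have 3 more visits than the rest. In YOU CALL that gap alone would create variance of 0.15 × 0.85 × 9 = 1.15, more than the total variance of 1 that the plan assumes.

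A separate analysis plan may add imputation or sensitivity analyses, and their absence here is not held against the article. The point concerns the comparison that the article does name.

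**Conclusion.** The point holds as a weak choice of primary analysis with a conditional bias. The named six-month comparison excludes people without a six-month value, and the stated response to expected loss maintains power only. At 5%/15% loss and a gap of 0.5 to 1 SD, the bias is about a sixth to a third of the visit target and about a tenth to a fifth of the QLI target. At 7.5%/12.5% it is about half that, and under balanced loss with equal gaps it is zero. These sizes rest on assumed loss rates and gaps, because the documents supply only the overall 10%. Nothing shows that bias will occur, and the sample size is not affected. The change is worth making because the better analysis uses data that the trial already plans to collect.

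**What to change.** 1. **QLI.** Make the primary estimate the six-month contrast from a likelihood-based mixed model that keeps every randomised participant with any post-baseline value (three, six or twelve months), adjusted for baseline QLI, comorbidity stratum and province. Allocation was stratified by the last two.
2. **Unplanned visits.** Use a count model with the log of calendar time observed as an offset, so that partial calendars contribute, adjusted for stratum and province.
3. **Sensitivity.** Add one analysis that shifts missing outcomes separately by arm, and report loss by arm.
4. **Wording.** Describe the t-test as an available-case analysis by allocated group.

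The cost is revised analysis text and a little more analysis work, with no change to recruitment or data collection. The mixed model relies on outcomes being missing at random. The offset assumes that the visit rate in unobserved months resembles that in observed months, whereas the protocol expects events to be more frequent early on. Participants with no post-baseline data enter neither model. The shift analysis shows how far the conclusions depend on these assumptions.
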